## Abstract

**Background:**

The optimal strategy for abdominal wall closure has been an issue of ongoing debate. Available studies do not specifically enroll patients who undergo emergency laparotomy and thus do not consider the distinct biological characteristics of these patients. The present randomized controlled trial evaluates the efficacy and safety of two commonly applied abdominal wall closure strategies in patients undergoing primary emergency midline laparotomy.

**Methods/design:**

The CONTINT trial is a multicenter, open label, randomized controlled trial with a two-group parallel design. Patients undergoing a primary emergency midline laparotomy are enrolled in the trial. The two most commonly applied strategies of abdominal wall closure after midline laparotomy are compared: the continuous, all-layer suture technique using slowly absorbable monofilament material (two Monoplus® loops) and the interrupted suture technique using rapidly absorbable braided material (Vicryl® sutures). The primary endpoint within the CONTINT trial is an incisional hernia within 12 months or a burst abdomen within 30 days after surgery. As reliable data on this primary endpoint is not available for patients undergoing emergency surgery, an adaptive interim analysis will be conducted after the inclusion of 80 patients, allowing early termination of the trial if necessary or modification of design characteristics such as recalculation of sample size.

**Discussion:**

This is a randomized controlled multicenter trial with a two-group parallel design to assess the efficacy and safety of two commonly applied abdominal wall closure strategies in patients undergoing primary emergency midline laparotomy.

**Trial registration:**

NCT00544583

## Background

In Germany, more than 700,000 open abdominal operations (laparotomies) are performed each year [1]. A major surgical complication after laparotomy is abdominal fascia dehiscence, which may appear either as an early (burst abdomen with evisceration) or a late (incisional hernia) complication. These patients usually undergo surgery for secondary fascial closure, which is associated with markedly increased morbidity [2], including high recurrence rates (up to 45%) [3]. The applied surgical strategy for abdominal wall closure (that is, the combination of suture technique and material) is of high relevance for the prevention of fascia dehiscence and, moreover, constitutes the main factor directly controllable by the surgeon. However, a recent cross-sectional study among surgeons at institutions participating in a large multicenter trial revealed a lack of consensus regarding abdominal wall closure strategies [4]. In particular, there is uncertainty regarding optimal abdominal wall closure in patients undergoing an emergency laparotomy. Several randomized controlled trials (RCTs) as well as meta-analyses have addressed the issue of optimal fascia closure in elective laparotomies [2,5-12]. Yet, there have been no RCTs dealing exclusively with the emergency setting. As a result, abdominal fascia closure is performed according to the surgeon’s individual preference rather than according to evidence-based data. The present RCT is designed to compare the most established strategies (continuous slowly absorbable sutures and interrupted rapidly absorbable sutures) for abdominal wall closure after midline incisions for emergency laparotomy to determine the superiority of either strategy regarding the development of incisional hernia.

## Methods and design

The CONTINT trial is a randomized controlled two-group parallel superiority trial. Figure 1 shows the study flow chart. Patients requiring an emergency primary midline laparotomy are screened for inclusion into the trial and randomized intraoperatively. The patients’ demographic data and medical history, antibiotic prophylaxis and/or therapy, intraoperative findings, cause of peritonitis, surgical management and source control will be reported. Furthermore, the time needed for fascial closure, length of fascia incision, length of remaining suture material (continuous group) or number of sutures needed (interrupted group) and the surgeon performing the abdominal wall closure will be documented.

**Figure 1 F1:**
[figure not shown]
Flow chart of the CONTINT trial.

In total, five visits are scheduled within the CONTINT trial (Table 1). Follow-up visits are carried out on day 30 after surgery (visit 4) and 12 months after surgery (visit 5). Follow-up data for visit 4 are collected by telephone interview only. Patients are asked study-related questions on pulmonary infection, wound infection or hernia. If necessary, the general practitioner carries out a clinical and ultrasound examination to detect a bulging hernial sac and palpable fascia gap. Quality of life is assessed using a validated questionnaire (SF 36® Health Survey), which has previously been used in trials on surgical interventions. On visit 5, a clinical and ultrasound examination is performed to assess the primary endpoint.

**Table 1 T1:** Course of examinations during the CONTINT trial

**Visit**	**1 ****(Screening)**	**2 ****(Operation)**	**3 ****(Day of discharge)**	**4 ****(30 days post operation)**	**5 ****(12 ± 1 months post operation)**
Demographics^a^ and baseline clinical data^b^	X	X			
Eligibility criteria	X	X			
Randomization, surgical intervention		X			
Clinical visit/telephone interview^c^			X	X	X
Quality of life^d^				X	X
Safety^e^		X	X	X	X

^a^Gender, date of birth, height (cm), weight (kg); ^b^smoking, diabetes mellitus, renal insufficiency, chronic pulmonary impairment, immunosuppressive treatment, anemia, malignant disease, American Society of Anesthesiologists score, Mannheim Peritonitis Index [13], indication, surgical intervention; ^c^clinical visit/telephone interview outcome assessment, ultrasound of abdominal wall (only visit 5); ^d^assessed by the Short Form (36) Health Survey (visit 4: by telephone); ^e^serious adverse events.

### **Patient recruitment**

The study protocol was approved by the Independent Ethics Committee, University of Heidelberg. All patients will be informed about the purpose of the CONTINT trial, the applied surgical strategies, and possible benefits as well as potential risks. Screened patients who have not been enrolled into the trial (including patients unable to give informed consent due to any reason) will be documented in the screening log, including the reason for non-inclusion. In order to be eligible for the trial, patients must be older than 18 years and have given informed consent when undergoing primary emergency abdominal surgery. Their expected survival time should be more than 12 months. Patients requiring primary midline laparotomy for ischemic or infectious disease may be included. While patients with a previous laparotomy are excluded, patients who had previously undergone laparoscopy (except for colon resections) or minor abdominal operations (for example, conventional appendectomy, cholecystectomy, hysterectomy, section) may be included. Furthermore, a septic abdominal focus (for example, perforated stomach ulcer, perforated diverticulitis) must be present.

In addition to these preoperative criteria, the septic source must be successfully controlled and abdominal lavage must be performed prior to intraoperative randomization. When a re-laparotomy is planned intraoperatively (that is, a second look operation), patients may not be included. Patients are excluded from the trial if they are already participating in another trial with interference of the intervention and outcome of this study.

### **Endpoints**

The primary endpoint of the CONTINT trial is a burst abdomen within 30 days postoperatively or an incisional hernia within 12 months after the surgery.

A burst abdomen is defined as postoperatively missing continuity of the abdominal fascia in combination with a wound dehiscence and/or a consecutive relapse operation occurring up to day 30 after surgery.

The endpoint ‘incisional hernia’ is assessed by a physical examination and an abdominal ultrasound examination at the trial center 12 months after the operation. A hernia is present if a fascia gap and a protruding hernia sac are seen on ultrasound and if the clinical examination is consistent with a hernia. To guarantee independence of the outcome assessment, the clinical and ultrasound examination needs to be performed by a board certified surgeon familiar with the examination of the abdominal wall, who has not been involved in the surgical procedure of the patient. Ultrasound examinations have to be carried out by an investigator who has had at least six months training in this method.When a patient’s hernia is confirmed by a surgical intervention for an incisional hernia within 12 months after the index operation, the primary endpoint is achieved even in absence of an ultrasound examination by the operation report.

A set of surgical and nonsurgical parameters will be documented as secondary endpoints within the CONTINT trial (Table 2).

**Table 2 T2:** Secondary endpoints within the CONTINT trial

**Secondary endpoint**	**Definition**
**Length of skin incision**	Length of wound from the upper to the lower pole of the skin (cm) after abdominal wall closure (skin staples in place)
**Length of fascia incision**	Length of wound from the upper to the lower pole of the fascia (cm) after closure of fascia
**Time needed for fascial closure**	From the first stitch to the last knot (min)
**Frequency of re-operation due to burst abdomen**	Surgical intervention indicated due to the occurrence of burst abdomen after intervention
**Frequency of re-operation**	Any laparotomy at any time during the follow-up period
**Frequency of abdominal re-interventions**	Any puncture of the abdominal cavity (for example, computed tomography- or ultrasound-guided drainage) at any time during the follow-up period
**Postoperative pulmonary infection**	Infection of the lung with either evidence of increased infection parameters (C-reactive protein > 2 mg/dl and/or leukocytes > 10,0000 cells/ml) that are not caused by a different pathologic process or evidence of pulmonary infiltration in the chest X-ray, requiring antibiotic therapy. Decrease of lung function testing results (forced expiratory volume in 1 s and vital capacity) by 20% or more in comparison with the baseline lung function testing.
**Duration of artificial respiration**	Time on the respirator postoperatively (days)
**Duration of postoperative hemodialysis**	Time on hemodialysis (days)
**Frequency of wound infection**	Surgical site infections within 30 days divided into superficial and deep incisional infections according to the Centers for Disease Control and Prevention definition [14]
**Duration of vacuum therapy**	From first placement of the sponge to removal of the sponge (days)
**Duration of wound healing in patients with secondary wound healing**	From opening of the wound to complete skin closure (days)
**Time to first bowel movement**	From the day of surgery until day of patient’s first bowel movement
**Quality of life**	SF 36 filled in by the patient 30 days and 12 months after the index operation
**Duration of abdominal drainage via intraoperatively placed drains**	From the day of surgery until the day of removal of the last intraoperatively placed drain (days)
**Duration of closed abdominal lavage**	From the day of surgery until the last day of closed abdominal lavage via the intraoperatively placed drains (days)
**Postoperative duration of hospital stay**	From the day of the operation until the day of discharge (days)
**Postoperative duration of intensive care unit stay**	Time from admission to the intensive care unit until transfer to the regular ward (days)
**Mortality**	Death due to any cause at any time during the follow-up period

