### **Standardized treatment**

Patients’ intraoperative and perioperative treatment is standardized except for the closure of the abdominal wall, which is carried out according to the allocated study intervention. Antibiotic prophylaxis and therapy is carried out according to local standards (for example, see [15]).

Electric cautery is used to cut skin, the subcutaneous tissue and the abdominal fascia, carefully avoiding damage to the umbilicus [16]. Opening of the abdomen is performed with scissors and incision of the peritoneum is completed with electric cautery. The performed surgical intervention depends on the underlying disease and is performed in line with local standards. In case of a septic focus (for example, a perforated diverticulitis or perforated gastric or duodenal ulcer), source control and abdominal lavage are essential parts of the procedures. Abdominal drains are placed at the end of surgery. Furthermore, drains may be placed for postoperative continuous lavage. Creation of a stoma is not an exclusion criterion for this trial.

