### **Assessment of safety**

Occurrences of events concerning the primary or secondary endpoints are assessed as endpoints only (not as adverse events) and are explicitly asked for.

The following conditions are expected after the initial operation and will therefore not be classified as a complication: pain, nausea, vomiting, urinary tract infection, hyper- or hypotension, imbalances of blood sugar or electrolytes and other laboratory values out of range, if they are not exceeding the duration and extent that can be expected after surgery.

From the day the patient has signed informed consent until the regular end of the trial at 12 months follow-up or until premature withdrawal of the patient, all serious adverse events (SAEs) must be reported within 5 days after the SAE is known. The SAE form contains the following information: identification of the trial participant, attending physician, description of the SAE (event, beginning and duration, severity, outcome, causality to the intervention of the trial, treatment or interventions taken), date and signature of the attending physician.

Analysis of safety-related data will be based on these SAE reports.

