#### ***Data analysis***

For the interim analysis as well as for the final analysis, each patient’s allocation to the different analysis populations (full analysis set (FAS), per protocol (PP) analysis set, safety analysis set) will be defined prior to the analysis. The allocation will be documented in the statistical analysis plan. During the data review, deviations from the protocol will be assessed as ‘minor’ or ‘major’. Major deviations from the protocol will lead to the exclusion of a patient from the PP analysis set.

The null hypothesis is assessed by testing the effect of the wall closure procedure (continuous versus interrupted) in a logistic regression model that takes into account the covariates body mass index (BMI; values as measured on the original scale) and age (values as measured on the original scale). The decision rules according to the adaptive design as specified above will be applied in the interim and the final analysis, respectively.

Confirmatory analysis will be primarily based on the FAS, which is consistent with the intention-to-treat principle by including all patients who were randomized to the two groups. This approach reflects the idea that the study should match as closely as possible to the conditions in clinical practice.

If a patient leaves the study prematurely, missing data with respect to the primary outcome variable will be replaced by the Imputed Case Analysis by incorporating available reasons for missing data (ICA-r) method described by Higgins *et al*. [22].

In addition to the evaluation of the FAS, a PP analysis will be performed for the primary endpoint including all randomized patients without major protocol violations. The secondary variables will be analyzed descriptively by tabulation of the measures of the empirical distributions and by application of appropriate tests whose results are to be interpreted in a strictly descriptive sense.

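### The re-operation endpoint counts every laparotomy in 12 months, so planned operations such as stoma reversal dilute, by an unknown amount, any contrast in unplanned re-operation

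*Protocol article*

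**What the plan says.** In the protocol article, Table 2 (section Endpoints) defines the frequency of re-operation as "Any laparotomy at any time during the follow-up period". No limit is set by indication, urgency or relation to the index operation. Table 1 places the last visit at 12 ± 1 months.

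Four other places bear on the point:

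- **Who is enrolled.** Patient recruitment requires that "a septic abdominal focus (for example, perforated stomach ulcer, perforated diverticulitis) must be present". Standardized treatment adds: "Creation of a stoma is not an exclusion criterion for this trial". Stoma reversal is not mentioned anywhere.
- **Planned re-laparotomy at entry.** Patient recruitment states: "When a re-laparotomy is planned intraoperatively (that is, a second look operation), patients may not be included". This is the only planned re-laparotomy that the article deals with.
- **Neighbouring rows of Table 2.** Re-operation for burst abdomen has its own row, defined as "Surgical intervention indicated due to the occurrence of burst abdomen after intervention". Abdominal re-interventions form another row, defined by puncture of the abdominal cavity, with image-guided drainage as the example.
- **Status of these events.** Assessment of safety treats primary and secondary endpoint events as endpoints and not as adverse events, and bases the safety analysis on SAE reports. Under Data analysis, secondary variables are tabulated and tested with methods "whose results are to be interpreted in a strictly descriptive sense".

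**The concern.** A re-operation rate is normally read as information on what went wrong after the index operation. Under the Table 2 rule it is a mixture of unplanned re-laparotomies and planned laparotomies done later in the year, with elective stoma reversal the obvious candidate in this population. Whether a stoma exists is settled before randomization, because patients are randomized just before closure of the abdominal wall. Planned reversals may therefore occur at similar rates in both arms and carry little information about the closure method.

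The Discussion suggests that interrupted closure might, in theory, lead to fewer intra-abdominal complications. An unplanned re-laparotomy for such a complication, without burst abdomen, would be counted only in the any-laparotomy row, where it cannot be told apart from a planned operation. Because endpoint events are kept out of adverse event reporting, the SAE data would not reliably supply the split.

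There is also a gap at the other edge of the definition. A laparoscopic re-exploration is not a laparotomy and is not clearly a puncture of the abdominal cavity, so its place in Table 2 is uncertain.

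**Working it through.** **The plan's own figures.** The article states no figure for re-operation. Its only power figure concerns the primary endpoint: 80% for early rejection with 80 evaluable patients, one-sided bound 0.0115. A pooled-variance chi-square calculation without continuity correction, 40 per group, gives 80.0% for 0.20 versus 0.53 and 82.1% for 0.30 versus 0.65. The overall one-sided level is 0.0115 + 0.0038 × ln(0.40/0.0115) = 0.02499, which agrees with the stated 0.025. None of these figures uses the re-operation endpoint.

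**Inputs for the dilution check.** All rates are assumptions, because the documents give none:

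- p = proportion of patients with at least one unplanned re-laparotomy: 10% in one arm, 25% in the other.
- q = proportion with a planned laparotomy within 12 months, taken as equal in both arms and independent of unplanned re-operation: 0% to 20%. For orientation, if 20–40% of patients had a stoma and half of these were reversed by laparotomy within the year, q would be 10–20%.
- 40 patients per arm, which is the 80 evaluable patients of the interim analysis split equally.

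**Formula.** A patient counts if either event occurs:

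observed rate = 1 − (1 − p)(1 − q) = p + (1 − p)q.

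The difference between arms is therefore (p₂ − p₁)(1 − q). The same q also raises both rates, so the ratio moves toward 1.

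At q = 10%: 0.10 + 0.90 × 0.10 = 0.19 and 0.25 + 0.75 × 0.10 = 0.325. The difference is 0.135 = 0.15 × 0.90, and the ratio is 0.325/0.19 = 1.71.

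| q | Observed rates | Difference (points) | Ratio | Power, 40 per arm, two-sided 5% |
|---|---|---|---|---|
| 0% | 10% vs 25% | 15.0 | 2.50 | 42% |
| 5% | 14.5% vs 28.75% | 14.25 | 1.98 | 34% |
| 10% | 19% vs 32.5% | 13.5 | 1.71 | 28% |
| 15% | 23.5% vs 36.25% | 12.75 | 1.54 | 24% |
| 20% | 28% vs 40% | 12.0 | 1.43 | 20% |

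The power column uses the normal approximation and serves only as a yardstick for lost information, since no power is claimed for this endpoint.

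**A second set of assumed rates.** With 10% versus 20% unplanned, the difference falls from 10 points to 9.5, 9, 8 and 7 points at q = 5%, 10%, 20% and 30%. The ratio falls from 2.0 to 1.66, 1.47, 1.29 and 1.19. The number per group needed for 80% power rises from 199 to 270, 348, 533 and 771.

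**Reading.** Under equal and independent q, the direction is the same for every choice of rates. The size depends entirely on q, which the documents do not give.

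**The case against.** The strongest reply is that an any-laparotomy count is objective, which has value in an open-label trial. It does what its label says, and it is one of many secondary rows with no alpha attached. The re-operation most closely tied to fascial closure, for burst abdomen, has its own row that a stoma reversal cannot enter. Image-guided drainage, the likely treatment of some fluid collections or abscesses, also has its own row. The CRF is not shown, and splitting a descriptive table by indication is often left to the CRF or the SAP.

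Much of this stands, and it limits the point. It does not remove it: the definition is stated rather than left open, and neither neighbouring row yields the count of unplanned re-laparotomies for reasons other than burst abdomen. Keeping the objective count beside an unplanned count also meets the concern about judgement.

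Two further objections are partly right:

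- **Equal and independent q is an assumption.** Stoma creation precedes randomization, but whether and when a stoma is reversed within the year may depend on recovery, wound complications or death, all of which follow randomization. If q differs between arms, the distortion need not be a simple dilution.
- **The laparoscopic gap is narrower than it looks.** If a laparoscopic re-exploration falls outside the endpoints, a serious complication behind it should still be reported as an SAE. It is then recorded, but not as a re-operation.

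A reader might infer from the exclusion of planned second looks that the endpoint was meant to capture unplanned events only. That exclusion is an entry criterion, and the article does not link it to the endpoint.

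**Conclusion.** The point holds as a weakness in the definition of one secondary endpoint. As written, the row cannot separate planned from unplanned laparotomies. Under an equal and independent planned rate q, it shrinks the absolute contrast in unplanned re-operation by the factor 1 − q and pulls the ratio toward 1. In the assumed 10% versus 25% example, the ratio of 2.5 becomes 1.98 at q = 5% and 1.43 at q = 20%. The actual dilution cannot be determined from the documents, and it is small if few reversals are done by laparotomy within the year.

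Two stronger readings are tempting and not supported:

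- **That stoma reversals are scored as complications.** The article counts them as re-operations, does not call the row a complication measure, and keeps endpoint events out of adverse events.
- **That a real difference is masked.** Dilution follows from the stated assumptions; concealment would need rates that the documents do not contain.

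The primary endpoint, its alpha and the sample size are untouched, and the re-operation result is to be read descriptively. The change is a cheap improvement worth making, not a condition for the validity of the trial.

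**What to change.** - **Record:** for each abdominal re-operation, enter its indication, whether it was planned or unplanned, and whether it was open or laparoscopic. The classification is made from the operation report by a person unaware of the allocation.
- **Define:** make unplanned abdominal re-operation during follow-up, open or laparoscopic, the Table 2 endpoint.
- **Report:** tabulate planned laparotomies, such as stoma reversal, separately by arm, and keep the any-laparotomy count as a supplementary row so that no information is lost.

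The cost is one CRF item, one revised definition and a simple classification judgement. No extra procedure or visit is needed. The article reports 73 patients randomized and 11 centers, so re-operations that have already occurred would be classified retrospectively from the operation reports.

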### **Trial interventions**

Before closure of the abdominal wall, the length of the fascial incision is measured (in centimeters)*.* Then, four Mikulicz clamps (or equivalent) are placed at the edges of the abdominal fascia. The expertise of the surgeon (board certified versus no certificate) present at the closure is documented.

In the continuous group, the abdomen is closed by a continuous, all-layer suture using two Monoplus® loops, which are made of a slowly absorbable monofilament material. Monoplus® sutures need to be stretched once by the assisting nurse or operation technician before use to avoid breakage of the material. The first stitch has to be anchored cranial and caudal of the incision. After having closed half of the wound, one end of the loop is cut right below the needle. Then one stitch is made back to the opposite edge of the fascia and both ends are tied with at least four counter-rotating knots. At the caudal end of the wound, the same procedure is done with intersection of both loops at the middle of the incision and overlapping of both suture lines for at least 2 cm. Loops are not to be tied together. For every patient, two loops must be used, irrespective of the length of the wound. After completion of the fascial closure, the loop will be cut directly underneath the needle. The length of the remaining suture material has to be measured.

In the interrupted group, patients will receive abdominal wall closure by interrupted sutures using Vicryl® sutures. Anchoring of stitches cranial and caudal of incision is performed in analogy to the continuous suture group. Suturing of the abdominal wall is performed from either end of the incision to the middle of the incision. The number of sutures used has to be recorded. Once all stitches are done, each suture is tied with at least four counter-rotating knots.

For both groups, the maximum distance between the stitches should be 1.5 cm and the distance from the edge of the fascia should be at least 2 cm. Subcutaneous tissue is not sutured and no subcutaneous drainage is used. The skin is closed with clips and the length of the skin incision (in centimeters) is measured*.*

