### **Randomization and blinding**

Patients will be randomized to one of the two treatment groups just before closure of the abdominal wall using sealed envelopes. Randomization numbers will be allocated to the two groups in balanced permuted blocks using the random number generator of the validated software SAS by the Institute of Medical Biometry and Informatics (IMBI), Heidelberg, Germany. To avoid any potential of predicting group allocation for patients, the block length is fixed in a separate document that is withheld from the study site. As performed in previous studies, sealed and opaque envelopes are produced and labeled with the randomization number containing a data sheet that states the group allocation for the patient with the respective randomization number [17-19]. Randomization envelopes will be used in consecutive order. To avoid manipulations, a thick black bar was placed on the opposite side of the sheet, exactly at the position where the randomization information is located. Basic characteristics of the patient and day of randomization are documented on the data sheet. Thus, compliance to the randomization scheme may be controlled retrospectively. When the study is finished, all unopened envelopes will be sent back to the data management center where they are compared to the allocated randomization numbers and checked for completeness.

The assessors of the CONTINT trial are blinded to the patients’ study treatment.

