Based on the described differences between patients undergoing emergency and elective laparotomy as well as the current lack of studies, there is an urgent need for prospective studies specifically assessing strategies of abdominal wall closure after emergency midline laparotomy The present RCT compares the two most commonly applied strategies of abdominal wall closure after midline laparotomy, that is, the continuous, all-layer suture technique using slowly absorbable monofilament material (two Monoplus® loops) and the interrupted suture technique using rapidly absorbable braided material (Vicryl® sutures). The incidence of burst abdomen by 30 days or incisional hernia within 12 months after surgery was chosen as the primary endpoint to specifically assess the impact of both closure techniques on abdominal fascia healing in the emergency setting. In theory, the interrupted closure technique may allow discharge of (contaminated) ascites and thus be associated with fewer intra-abdominal complications (for example, fluid collections or abscess) as well as improved abdominal fascia healing. However, a randomized trial is required to validly assess superiority of this technique.

An adaptive interim analysis is performed in the CONTINT trial to cope with the lack of reliable data required for a substantiated sample size calculation.

To achieve a homogenous study population, only patients undergoing primary midline laparotomy for an emergency indication will be included in the CONTINT trial. Furthermore, the confirmatory analysis of the overall treatment effect is performed using a logistic regression model that includes patients’ BMI and age as potential confounding factors. There is a recognized need to standardize the definition of complications after surgical interventions to enable comparisons of results from different studies [29-31]. For this reason, endpoints within the CONTINT trial have been defined *a priori* to minimize assessment bias.

In conclusion, the CONTINT trial represents the first RCT assessing efficacy and safety of two different abdominal wall closure strategies in patients undergoing emergency midline laparotomy. Applying high methodological standards, the results of the trial will help to improve and standardize surgical treatment in this specific population of patients that may not be simply compared to patients undergoing elective surgery.

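### Wound-healing time is tested between arms only among patients whose wound opened after randomization, so the test is not a randomized comparison and can favour the arm with more open-wound days

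*Protocol article*

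**What the plan says.** In the Endpoints section of the protocol article, Table 2 names the endpoint "Duration of wound healing in patients with secondary wound healing" and measures it as "From opening of the wound to complete skin closure (days"). The restriction to a subset is part of the endpoint's name, so it is not a detail left to an analysis plan. No value is given for a patient whose wound never opened.

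The order of events is fixed elsewhere. Under Randomization and blinding: "Patients will be randomized to one of the two treatment groups just before closure of the abdominal wall using sealed envelopes". Under Trial interventions, for both groups: "The skin is closed with clips and the length of the skin incision (in centimeters) is measured". Any wound opening therefore follows allocation.

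Under Data analysis, the secondary variables are tabulated and also analysed "by application of appropriate tests whose results are to be interpreted in a strictly descriptive sense".

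Table 2 lists neither the frequency of wound opening nor open-wound days in all patients. The nearest companion is wound infection: "Surgical site infections within 30 days divided into superficial and deep incisional infections".

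**The concern.** A comparison of durations among opened wounds is protected by randomization only if the closure strategy has no influence on whose wound opens. The article gives reasons to expect that it may. The Discussion says that the interrupted technique may in theory "be associated with fewer intra-abdominal complications (for example, fluid collections or abscess) as well as improved abdominal fascia healing". It also describes bacterial growth in tissue as a risk factor for wound infection, delayed wound healing and dehiscence. Burst abdomen, a component of the primary endpoint, is defined partly through wound dehiscence, so the trial's own hypothesis allows for a difference between the arms in events of this kind.

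If membership differs by arm, the two subsets contain different kinds of patient. Patients with the best outcome, those with no open wound, contribute nothing. At stake is the direction of one reported secondary result: an arm that adds minor openings dilutes its own average and may be reported as healing faster.

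**Working it through.** The plan states no figure for this endpoint, so there is nothing of its own to reproduce. The check asks when the subset comparison and the all-patient comparison point in opposite directions, and by how much.

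**Inputs from the article.** Subset, clock, timing of randomization and planned tests, as above. The interim analysis has 80 evaluable patients, taken here as 40 per arm.

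**Assumptions, not in the article.** In both arms 25% of wounds open and heal in a mean of 40 days. Arm B has a further fraction q of patients with openings that heal in a mean of d days.

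**Formulas.**
- Subset mean: A = 40; B = (0.25 × 40 + q × d) / (0.25 + q). Difference B − A = q(d − 40) / (0.25 + q).
- Open-wound days per randomized patient, 0 if never opened: A = 0.25 × 40 = 10; B = 10 + q × d. Difference B − A = q × d.

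For q > 0 and d below 40, the first difference is negative (B looks better) and the second is positive (B is worse). At d = 40 the subset means tie. Above 40 both differences show B as worse. At q = 0 both are zero.

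| q | d (days) | Subset mean, B | Subset difference | Per-randomized difference | Simulated tests with p < 0.05 favouring B |
|---|---|---|---|---|---|
| 0.25 | 12 | 13.0/0.50 = 26.0 | −14.0 | +3.0 | 49–51% |
| 0.25 | 20 | 15.0/0.50 = 30.0 | −10.0 | +5.0 | 28% |
| 0.25 | 30 | 17.5/0.50 = 35.0 | −5.0 | +7.5 | 10% |
| 0.10 | 12 | 11.2/0.35 = 32.0 | −8.0 | +1.2 | 16–17% |
| 0.10 | 20 | 12.0/0.35 = 34.3 | −5.7 | +2.0 | 10–11% |
| 0.05 | 12 | 10.6/0.30 = 35.3 | −4.7 | +0.6 | 7% |
| 0.05 | 20 | 11.0/0.30 = 36.7 | −3.3 | +1.0 | 5% |
| 0 | – | 40.0 | 0 | 0 | 2% |

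The last column is from simulations of 2,000 to 4,000 trials with 40 patients per arm, gamma healing times (shape 4) and a two-sided Mann-Whitney test in the subset.

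**Hand check with fixed counts, also assumed.** Arm A has 8 of 40 wounds open for 40 days each. Arm B has the same 8 plus 8 that heal in 14 days. Subset means: 320/8 = 40.0 against (320 + 112)/16 = 27.0. Per randomized patient: 320/40 = 8.0 against 432/40 = 10.8. If the 8 added wounds took 50 days instead, B's subset mean would be (320 + 400)/16 = 45.0, and B would correctly look worse.

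**Does a median help?** No. In the strongest scenario (q = 0.25, d = 12) the subset median was 17.4 days lower in arm B.

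**The case against.** The strongest reply has four parts.

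1. *The endpoint is secondary and its tests are labelled descriptive.* This stands as far as it goes. The primary analysis, the stopping rules and the sample size do not use it. But the label deals with confirmatory status; it does not make the two subsets comparable.

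2. *An excess of openings would be visible elsewhere.* In part. Wound infection is recorded in all patients, burst abdomen is counted separately, and a table of durations would show how many wounds opened. In the strongest scenario about 10 against 20 opened wounds would be expected, and a Fisher test on those counts was significant in 58% of simulated trials. However, wound infection stops at 30 days, and openings without infection have no listed frequency.

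3. *The reversal depends on invented rates.* It does. A reader might infer that the rule will reverse the result, or that about half of such trials would wrongly favour the worse closure. The article does not support that. The figure of about 50% belongs to one strong scenario, in which openings double and every added wound heals in under a third of the usual time. Milder scenarios give about 5% to 28%.

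4. *How long an opened wound takes to close is a legitimate question.* It is, as a description. That argues for keeping the tabulation, not for testing it between arms.

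A reader might also extend the criticism to vacuum therapy, which is measured "From first placement of the sponge to removal of the sponge (days"). The text does not support this. That row says how days are counted and names no population, so scoring untreated patients as 0 days is compatible with it.

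**Conclusion.** The point holds for the wound-healing row. The endpoint is restricted by name to a group formed after randomization, and a between-arm test on it is planned. That test is not a randomized comparison.

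The direction of the result can reverse, but only if one closure adds openings and these heal faster than the others. Under the assumed 25% baseline at mean 40 days, 10 to 25 points of added openings at mean 12 to 20 days shift the subset mean by about 6 to 14 days in that arm's favour, while it has about 1 to 5 more open-wound days per randomized patient. The true size is unknown, and the bias is absent if closure does not affect opening. It should be corrected because correction is cheap, not because the trial's main conclusion is at risk.

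**What to change.** - Define open-wound days for all randomized patients up to a fixed horizon, with 0 for a wound that never opened. State a rule for death, since an early death would otherwise score as few open-wound days, and a rule for wounds still open at last follow-up. Apply the between-arm test to this variable.
- Report the frequency of wound opening by arm.
- Keep duration among opened wounds as a tabulated description without a test.
- For vacuum therapy, state that untreated patients count as 0 days. This is a clarification only.

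Cost: a change of wording. The existing definition already needs the dates of opening and closure. The downside is a variable with many zeros, so a rank test or a bootstrap interval for the mean is needed, and power is modest: in the strongest scenario the all-patient rank test detected the harm in about 44% of simulated trials. In the scenarios with 10 or 25 points of added openings at 12 or 20 days, it favoured the worse arm in under 1%.
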